## Abstract

**Background:**

Chronic wounds impose a significant burden on patients and caregivers because of complications such as pain, infection, and repeated trips to and from hospitals. These challenges are compounded by prolonged healing times and substantial socioeconomic costs, particularly in aging populations and resource-limited settings. The Digitally Enabled Home-Based Wound Care (DE-HBWC) program facilitates the organization of home visits by caregivers through electronic devices and internet platforms, enabling patients to easily receive medication changes and treatments, thus allowing patients to continue to reside in familiar surroundings while enjoying the same treatment as they would in a hospital. The construction of DE-HBWC programs for chronic wound patients in China is hampered by a lack of scientific theoretical guidance and high-quality research. The PEDALs (Problem, Evidence, Determinants, Actions, Long-term, Scales) model, a theoretical framework used in implementation research, as a rational framework for the DE-HBWC program in this study. Unlike conventional approaches, the PEDALs model emphasizes iterative adaptation and long-term scalability, ensuring alignment with real-world clinical needs and technological advancements.

**Methods:**

We designed a combined quantitative and qualitative study consisting of five phases and one monitoring step, following the PEDALs model. In Phase I, the clinical problem was defined as wound management challenges in patients with chronic wounds. In Phase II, a literature review and evidence-based practice were undertaken to address the research questions. In Phase III, in-depth interviews will be conducted to identify barriers and facilitators to the implementation of the DE-HBWC program in chronic wound patients. In Phase IV, the DE-HBWC intervention protocol will be developed and followed by a randomized controlled trial of the DE-HBWC intervention program. In Phase V, a DE-HBWC implementation plan that is sustainable over the long term will be developed to promote its use. Monitoring of the implementation of interventions in phases III to V will be conducted.

**Discussion:**

This study evaluated the impact of the DE-HBWC program on wound healing and quality of life in chronic wound patients and to assess its economic benefits. The findings are expected to help resolve challenges faced by patients with chronic wounds attending hospitals for wound care.

**Trial registration:**

Prospectively registered at the Chinese Clinical Trials Registry on 24.12.2023, ChiCTR2300079030.

## Introduction

Skin diseases can cause severe non-fatal disabilities worldwide, especially in resource-scarce areas, affecting nearly one-third of the world’s population (1, 2). Increasing research on skin diseases, with the aim of providing high-quality care, is crucial for alleviating the burden of skin diseases (2). Skin and subcutaneous diseases are the fourth leading cause of non-fatal disease burden, accounting for 1.79% of the global disease burden (1). Chronic wounds are wounds that have not healed or shown no signs of healing for more than 1 month because of various factors; such wounds include vascular ulcers, diabetes foot ulcers, pressure ulcers, and chronic infectious wounds (3). The incidence rate of chronic wounds caused by various etiologies in the general population is 2.21‰, with leg ulcers having the highest incidence rate of about 1.51‰ and chronic wound patients increasing at a rate of 10% per year (4, 5). Chronic wounds mainly occur in the older adult population, and are associated with a series of complications and medical expenses (6). Chronic wounds cost over 25 billion US dollars in medical expenses annually, with 5% of the total medical expenses used for wound repair (3). Owing to complications such as pain, infection, amputation, and repeated visits to hospitals for medical treatment, chronic wounds impose a significant burden on patients’ personal, family, economic, and social well-being (6, 7). It is expected that chronic wounds will continue to be a major clinical, social, and economic challenge owing to the aging population, continuing global threat of diabetes and obesity, and the persistent emergence of drug-resistant infections. Addressing public health issues related to chronic wounds requires multiple approaches, including prevention, improving wound care management, and addressing potential risk factors (8). In the long run, the development and expansion of remote home care for chronic wound patients may enable a larger patient population to be targeted and improve their compliance with treatment (9, 10).

Emerging digital health technologies, such as remote monitoring and artificial intelligence (AI)-driven wound imaging, hold transformative potential for decentralizing care (11). However, their integration into structured home-based programs remains underexplored, particularly in the context of chronic wound management (12). Research indicates that these technologies can yield significant economic and health benefits, including reduced infection risk, enhanced patient mobility, cost savings, and improved clinical outcomes (13–15). With advancements in mobile electronic facilities and internet technology, electronic-based home care has been successfully implemented for patients with various conditions, including chronic wounds (16, 17). The Digitally Enabled Home-Based Wound Care (DE-HBWC) program represents an innovative intervention that combines telehealth technology with home care approaches. It enables caregivers to conduct home visits via electronic devices and internet platforms, allowing patients to receive medications and treatments conveniently. This not only reduces hospitalization costs but also enables patients to remain in familiar surroundings while receiving comparable care to that provided in hospitals. However, in China, the DE-HBWC program for patients with chronic wounds is still in the initial stage of exploration, and further research is needed (18). The primary objectives of this approach are to alleviate the burden of hospital visits, improve continuity of care, and enhance treatment outcomes through real-time monitoring and data-informed decision-making.

Interventions in clinical nursing research are often controversial owing to the lack of scientific theoretical support. As an emerging discipline, implementation science is aimed at promoting the application of evidence-based intervention programs in practice. In recent years, such programs have received increasing attention in various research fields. Their implementation helps to transform theoretical possibilities into practical applications, thus addressing the challenge of implementing validated intervention measures in the real world (19, 20). In 2013, the World Health Organization recommended the application of implementation studies in the field of healthcare, clarifying which interventions are effective and the reasons for their success or failure during implementation, in order to ensure that interventions operate optimally in the real world (20). Some nursing scholars have also attempted to apply commonly used theoretical frameworks of implementation science to nursing research, narrowing the gap between knowledge and practice, confirming the practicality of interventions and optimizing valuable nursing resources. Nurses can also establish a solid evidence foundation for nursing clinical practice (21). The PEDALs model (22) is a new research theoretical framework in the field of implementation research. It was first proposed by [name] team and applied in diabetes sharing outpatient service and influenza vaccination programs. The basic steps of the PEDALs model are as follows: Phase I: P (Problem) is a real dilemma; Phase II: E (Evidence) refers to evidence-based practice for solving difficulties; Phase III: D (Determinants) is the determining factor for implementing evidence-based practice, including obstacles and promoting factors; Phase IV: A (Actions) are implementation strategies that promote evidence-based practices; Phase V: Long term (L), refers to a plan for continuous implementation; and Scale(s) is the monitoring and evaluation of the research process. The first letter of each of these steps gives rise to the acronym PEDALs. The PEDALs model was selected for its structured yet flexible approach to addressing implementation challenges in digital health. Unlike Consolidated framework for implementation research (CFIR) (23), which provides a static taxonomy of determinants, PEDALs integrates problem identification, evidence synthesis, and iterative adaptation into a cohesive workflow. This is critical in chronic wound care, where interventions must adapt to evolving patient needs and technological advancements. Few nursing-related studies based on the PEDALs model have been reported, both in China and other countries. Therefore, application of this theory to help nursing staff conduct implementation research more effectively in real-world situations, and to make the research process and results more scientific, would represent a novel step in this field.

Therefore, this study utilizes a mixed-methods approach to construct a digitally enabled home-based chronic wound care project for chronic wound patients based on the PEDALs model, and to evaluate the effectiveness of this project in chronic wound patients at home using a randomized controlled trial approach.

## Methods/design

### Design

Our goal was to develop a DE-HBWC program for patients with chronic wounds, using scientific research methods. The study was a prospective study with a multi-stage mixed-methods design combining qualitative and quantitative research, following the five steps of the PEDALs model research paradigm (Figure 1). Qualitative methods included face-to-face one-on-one semi-structured interviews, literature review, and meetings with experts. The quantitative method comprised a parallel, two-armed randomized controlled trial design, with a 1:1 allocation ratio between the test and control groups for allocation concealment as well as blinding of assessors and statistical analysts.

**Figure 1 fig1:**
[figure not shown]
Flow diagram of the study design.

### Setting

This study will be conducted at Fujian Provincial Hospital, Fuzhou City, Fujian Province, China, which is one of the largest tertiary hospitals in Fujian Province, with highly developed facilities, platforms and staff support.

### Methods

This study followed the five steps of the research paradigm of the implementation science PEDALs model.

#### Phase I: Problem

Based on their clinical work, wound clinic healthcare professionals have identified many real-life challenges facing homebound chronic wound patients, such as long wound treatment cycles requiring frequent trips to the hospital, inconvenient access to medical care owing to the impact of their wounds, high pressure on hospital outpatient clinics who are unable to fully satisfy the demand, and long waiting times for medical care, among others. There is an urgent need to take measures to solve patients’ difficulties in accessing medical care and to alleviate the burden on their families. The digitally enabled home-based wound care program offers a way to solve these problem; however, such programs are still at the exploratory stage in China and most hospitals do not provide them. It is therefore, necessary to construct an evidence-based implementation DE-HBWC program for chronic wound patients and to explore the effectiveness of its application.

#### Phase II: Evidence-based practice

Evidence-based practice (EBP) refers to methods that combine individual clinical expertise with the best clinical evidence available from systematic studies (24) and patient values to achieve optimal health outcomes. EBP requires nurses to quickly access and evaluate evidence before integrating it into clinical practice (25). Two graduate nursing students were assigned to conduct a literature review in order to critically evaluate and summarize the evidence for development of a DE-HBWC program for patients with chronic wounds.

A comprehensive search strategy was executed across three international databases (PubMed, EMBASE, Web of Science) and three Chinese databases (China National Knowledge Infrastructure [CNKI], Wanfang Database, VIP Database for Chinese Technical Periodicals), covering peer-reviewed articles published between August 2014 and August 2024. The search employed the following Boolean operators and MeSH/Emtree terms: [(home-based) OR (home care services) OR (hospital at home) OR (telehealth*) OR (mHealth*) OR (telecare) OR (eHealth*) OR (telemedicine) OR (digital health*) [AND] (wound care) OR (chronic wounds)]. Filters restricted results to title/abstract fields and journal articles. Additional studies were identified through backward reference tracking (snowball method). Reference tracking was carried out to identify additional potentially relevant references. The inclusion criteria were studies with designs such as randomized controlled trials (RCTs), cohort studies, and quasi-experimental studies, and those published in English or Chinese. The exclusion criteria were non-peer-reviewed sources like conference proceedings, magazines, news articles, theses, dissertations, abstracts, editorials, systematic reviews, as well as gray literature such as technical reports and unpublished data.

#### Phase III: Determinants

This step entails the identification of determinants of implementation, including facilitators and barriers. CFIR is one of the most commonly used theoretical frameworks in implementation science, and comprises a menu of structures related to effective implementation to guide or evaluate the implementation of evidence-based practices. CFIR was first proposed by Damschroder et al. in the United States in 2009 and updated in 2022 as the Consolidated Framework for Implementation Research version 2.0 (CFIR 2.0) (23, 26). The theoretical framework consists of five domains, namely, the innovation domain, outer setting domain, inner setting domain, individuals domain, and implementation process domain. In this study, we applied the CFIR 2.0 framework and combined findings from the literature with clinical practice to identify interview questions for chronic wound patients, patient caregivers, wound specialty nurses, and healthcare facility administrators, addressing internal and external factors. Furthermore, we conducted in-depth interviews with these four groups using a semi-structured interview method. Researchers interviewed 10 chronic wound patients, 10 caregivers, 8 wound specialty nurses, and 5 healthcare facility administrators, each for 30–45 min. Table 1 shows the interview guides. Then, we identified barriers and facilitators to the implementation of the DE-HBWC program in patients with chronic wounds according to the CFIR 2.0 framework.

**Table 1 tab1:** Interview guides based on CFIR 2.0 framework.

Domain	Innovation	Outer setting	Inner setting	Individuals	Implementation process
Chronic wound patients					
Questions	How would you describe your experience using the digital tools (e.g., AI wound assessment app) for home-based care? What challenges, if any, did you face while using these tools?	How easy or difficult is it for you to access healthcare resources (e.g., supplies, specialists) in your community? Has your family or social network supported your participation in this program?	How well do you feel your care team (nurses, doctors) communicates with you about your wound care plan?	What motivates you to follow the remote monitoring schedule? Have you ever felt hesitant to use the technology? If so, why?	What suggestions do you have to make this program more patient-friendly?
Patient caregivers					
Questions	How has using digital tools (e.g., telehealth platforms) changed your caregiving routine? What features of the program have been most helpful or frustrating?	Are there community resources (e.g., support groups, transportation) that could better support your caregiving role?	How clearly do healthcare providers explain the care plan to you? Do you feel equipped to handle emergencies (e.g., sudden wound deterioration)?	What concerns do you have about balancing caregiving with other responsibilities?	How could the program better involve caregivers in decision-making?
Wound specialty nurses					
Questions	How does the digitally enabled home-based wound care program fit into your current workflow? What adjustments are needed to improve the usability of digital tools (e.g., AI reporting)?	How do local policies or insurance coverage affect your ability to deliver home-based care?	What organizational resources (e.g., training, staffing) are critical for successful program implementation? Are there communication gaps between your team and primary care providers?	How confident do you feel using telehealth platforms for wound assessments?	What strategies would ensure long-term sustainability of this program?
Healthcare facility administrators					
Questions	How does this program align with your institution’s strategic goals?	What external partnerships (e.g., insurers, tech companies) are needed to scale this program?	What financial or staffing investments are required to maintain the program? How do you measure the program’s success (e.g., cost savings, patient outcomes)?	How do staff attitudes toward technology influence program adoption?	What policy changes would improve the program’s integration into routine care?

#### Phase IV: Action

Action refers to the implementation of a strategy or intervention. This step was based on literature research results and identification of the determining factors for implementation to develop the initial draft of the DE-HBWC intervention plan. An expert meeting is held to revise the intervention plan, and 10 chronic wound patients are recruited for a one-month small-sample pre-experiment to create an applied version of the intervention plan. Participants in the expert meeting included 10 experts specializing in hospital management, wound specialist nursing, wound specialist physicians, information engineering technology and implementation science. Eligibility criteria will require all participants to hold a master’ s degree or higher and possess an associate senior-level professional title or equivalent. Subsequently, a randomized controlled trial of the DE-HBWC intervention plan will be conducted. The main content of the randomized controlled trial is described.

### Recruitment and screening of participants

The participants will be adult patients (aged at least 18 years) with chronic wounds and at least one experience of visiting a wound treatment clinic. To ensure positive and successful registration, we will adopt a proactive recruitment strategy. Participants will be recruited by placing posters at Fujian Provincial Hospital and creating electronic posters that will be shared and promoted by research team members and hospital staff on social media platforms such as WeChat (one of the most widely used chat apps among Chinese citizens). Specialized nurses in wound treatment clinics will actively promoted recruitment of patients who attend for treatment, search for their electronic medical records, and perform other related tasks. Potential participants who respond to the recruitment strategy and contact the researchers will be screened in person or over the phone. The research purpose and process will be carefully explained to participants who met the inclusion and exclusion criteria. Patients who agree to participate will be recruited after signing an informed consent form and completing a general information survey and baseline data survey.

### Inclusion criteria

Patients are eligible for inclusion if they meet all of the following eligibility criteria: (1) age≥18 years; (2) histologic criteria of the Chinese Medical Association for chronic wound (27); (3) the duration of wound was 1 month or more; (4) the patient or an accompanying person has the ability to operate a smartphone; and (5) provision of informed consent and a signed informed consent form.

### Exclusion criteria

Patients who meet any of the following criteria will be excluded: (1) receiving palliative care or having malignant or fungal tumors, wounds with blind-end tracks such as sinus tracts, dry gangrene, exposed blood vessels, and other non-healing wounds; (2) suffering from mental illness or not cooperating with care; (3) suffering from autoimmune diseases or other serious comorbidities; and (4) hospitalized patients.

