#### Criteria for discontinuing or modifying allocated interventions

Every participant has the right to withdraw from the trial at any time. Participants will be terminated from the trial if, in the opinion of the investigator, it is necessary to do so for any reason, including ineligibility, adverse events, withdrawal of consent. Participants randomly assigned to the intervention group had the option of participating in traditional hospital wound treatment in the control group if they did not want to continue with the intervention. If a participant withdraws due to a related adverse event, the investigator will schedule a follow-up visit or phone call until the adverse event is resolved or stabilized. Adverse events unrelated to the intervention will be followed up until completion of the trial. Participants who stop the trial will have anonymized data collected until the exit time point. Any assessments not completed will be considered missing data. The reason for withdrawal will be recorded. Participants who withdraw after being randomized will not be replaced. Participants found to be ineligible after randomization will be withdrawn and no further data will be collected thereafter.

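### Stopping data collection on patients found ineligible after randomisation conflicts with the intention-to-treat analysis, and an undefined exclusion widens the risk

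*Protocol article*

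**What the plan says.** In the protocol article, *Criteria for discontinuing or modifying allocated interventions* sets the rule for late findings of ineligibility: "Participants found to be ineligible after randomization will be withdrawn and no further data will be collected thereafter". The same section leaves termination to judgement, and ineligibility is among the reasons it names: "Participants will be terminated from the trial if, in the opinion of the investigator, it is necessary to do so for any reason". On data it says "Participants who stop the trial will have anonymized data collected until the exit time point" and "Any assessments not completed will be considered missing data". Withdrawn patients are not replaced.

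*Data collection and statistical analysis* declares an intention-to-treat analysis. It plans two-group tests and a repeated-measures mixed model, and mentions imputation of missing data (random forest) only among sensitivity analyses.

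*Exclusion criteria*, item 1, lists particular wound types and ends with "exposed blood vessels, and other non-healing wounds". The *Introduction* defines the target condition: "Chronic wounds are wounds that have not healed or shown no signs of healing for more than 1 month". *Inclusion criteria* require "histologic criteria of the Chinese Medical Association for chronic wound" and that "the duration of wound was 1 month or more".

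**The concern.** Intention-to-treat needs outcomes on everyone randomised, whatever is later learned about eligibility. A rule that stops outcome collection because of a judgement made after allocation works against that. The judgement has no time limit, no restriction to baseline evidence and no blinded adjudication.

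Late findings are foreseeable. Screening may be done by telephone (*Recruitment and screening of participants*). The weekly remote assessments in the intervention arm record sinus tract features, although sinus tracts are an exclusion. Contact also differs by arm: weekly video with biweekly home visits against clinic attendance every other day. Ineligibility could therefore be noticed at different rates in the two arms.

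The open-ended exclusion adds to this because it has no baseline definition. If a judgement about non-healing could be made after allocation, withdrawal could be related to the outcome. The stake is bias in the comparison of healing, more than loss of power.

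**Working it through.** **1. The withdrawal rule against the analysis principle.**
- Data up to exit are kept and later assessments count as missing. Withdrawn patients are therefore not said to leave the analysis set; their later outcomes are simply never observed.
- Healing duration is part of the primary outcome, and healing time is the sample-size quantity. A patient withdrawn before healing has no value for it and cannot enter a two-sample comparison of healing times.
- Biweekly wound scores before exit can still enter the mixed model, so that analysis is affected less.
- Imputation is confined to sensitivity analyses. The main healing-time comparison would rest on those not withdrawn.

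**2. The exclusion against the population.**
- Literal reading: an eligible wound has lasted at least a month without healing, so a bar on non-healing wounds excludes the patients sought.
- Reading in context: after tumours, sinus tracts, dry gangrene and exposed vessels, the phrase can mean other wounds not expected to heal. The text does not say so, and that reading is an undefined prognosis about healing.

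**3. The plan's own figure.** Inputs from *Sample*: means 38.64 and 32.54 (difference 6.10), SD 8.21, 5% type I error, 90% power. *Data collection and statistical analysis* makes the test two-sided.
- Two-sample t-test, equal variances, noncentral t: 40 per group, power 0.907. This reproduces the plan.
- Dropout: 40/(1 − 0.20) = 50 per group, 100 in total. This also reproduces.
- Losses at random cost little: power is 0.936 with 45 per group and 0.907 with 40, with no bias.

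**4. Hypothetical illustration of selective loss.** Assumptions not in the documents: normal healing times, no true difference, and loss of exactly the slowest healers from one arm only.
- Closed form: removing the slowest fraction p shifts the mean by SD × φ(z)/(1 − p). For p = 0.05: 8.21 × 0.1031/0.95 = 0.89, and 0.89/6.10 = 15%. For p = 0.10: 8.21 × 0.1755/0.90 = 1.60, and 1.60/6.10 = 26%.
- Simulation (40,000 trials, 50 per group, k slowest removed from the intervention arm, t-test on the rest):

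| k removed | Shift in mean | Share of 6.10 | Type I error |
|---|---|---|---|
| 0 | 0.0 | 0% | 5.1% |
| 1 | 0.4 | 6% | 5.9% |
| 3 | 1.0 | 17% | 10.5% |
| 5 | 1.5 | 25% | 17.6% |
| 10 | 2.8 | 46% | 42.7% |

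The article gives no unit for healing time, so the shifts are in the plan's own unstated unit.

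**The case against.** A reader might infer that the plan lets staff reclassify slow healers as ineligible and drop them from the analysis. The documents do not support that.
- The named wound types are features visible at presentation. Table 2 marks the exclusion criteria once, at week 0, and *Recruitment and screening of participants* applies them before consent.
- *Intervention, DE-HBWC arm* foresees wounds unhealed at 12 weeks and lets the intervention continue if the patient wishes. Non-healing is an expected course, not grounds for reclassification.
- Data to exit are kept, intention-to-treat is declared, and no section removes withdrawn patients from the analysis set.
- Intervention staff are unblinded, but the article does not say who rules on late ineligibility. Data collectors and statisticians are blinded.
- The figures illustrate arbitrary truncation. If the unit is days, 12 weeks is 84 days, and (84 − 38.64)/8.21 = 5.5 SD above the larger mean. That model contains essentially no wounds unhealed at 12 weeks.

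All of this stands, and it rules out the stronger reading. It does not answer two points. Outcome collection still stops on randomised patients after an unconstrained judgement, whatever the ground of ineligibility. The closing phrase of the exclusion also remains undefined; a full protocol might define it, but as printed it cannot be squared literally with the article's own population.

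**Conclusion.** The point holds in limited form. The stop on data collection after a late finding of ineligibility conflicts with the intention-to-treat analysis and falls most directly on healing time. The undefined exclusion increases the risk, since nothing confines its use to baseline. Outcome-related withdrawal is permitted by the wording, not prescribed by it.

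The size is unknown because the documents give neither the number of such withdrawals nor their split by arm. Random loss within the 20% allowance would leave power at about 90% or more and cause no bias. Selective loss from one arm could bias the comparison materially, but the tabulated values are hypothetical and should not be quoted as an estimate. The planned sample size is unaffected.

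**What to change.** 1. In *Criteria for discontinuing or modifying allocated interventions*, continue outcome collection at the scheduled visits for every randomised patient who still consents, including those later found ineligible, and analyse them in the arm assigned. This concerns data only; treatment after such a finding remains a clinical matter.
2. Confine any exclusion of ineligible patients to a sensitivity analysis, based only on information recorded before randomisation and judged blind to arm and outcome.
3. The sponsor should reconcile *Exclusion criteria* item 1 with the *Introduction* and *Inclusion criteria* by stating the closing phrase as features recorded before allocation. Which wounds to exclude is the sponsor's clinical decision.

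The cost is a wording change in two sections and continued follow-up of what should be a few patients at existing visits. The sample size stays at 50 per group.
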